### Sample size

The sample size is estimated for linear mixed effects modeling with two conditions, three repeated measures, and clustered data. Based on a pilot study among caregivers in a care center, means and standard deviations can be estimated for empathy, self-efficacy, and knowledge. The desired power is set to a minimum of 0.90 and α = .05. The three care centers are taken into account as clusters with intra cluster correlation of .2. We estimate that around 90 participants are needed to detect a main effect of 0.5 SD on the primary outcome measures. To correct for attrition, we increased the highest number by 10%, bringing the total number of participants to 100 parents/relatives and 100 professional caregivers.

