### Randomization

Cluster randomization among locations of the care centers will be used to prevent crossover effects between professionals and parents/relatives. Group homes and activity centers will be randomly assigned to the treatment condition or the care-as-usual condition by an independent party, based on order of entry and a pre-determined order of treatment conditions. Randomization of participants will occur after enrollment but before the baseline assessment. Participants are to be informed of their allocated condition shortly after T0 to reduce any response bias during the baseline assessment.

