### Measures

#### Demographics (T0)

At T0, the participants will answer questions on demographic characteristics, such as age, sex, level of education, work experience, and the relationship to the person with ID.

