### Data analysis

All statistical analyses will be conducted using SPSS version 23 [46]. Both groups of participants (parents/relatives and professionals) will be treated as separate groups in the analyses because we expect that matching will not be possible. Partial intention-to-treat analyses will be performed: participants will be excluded from the analysis if fewer than two data points are available. All other participants will be analyzed according to their assigned condition.

For social validity, empathy, and self-efficacy, average item scores will be reported for each questionnaire. For the knowledge test, the total number of correct answers is to be used. Reliability statistics (Cronbach’s alpha) will be reported for the knowledge test at T0, T1, and T2.

Descriptive statistics will summarize the characteristics of the participants. Demographic variables are recorded as categorical variables, so chi-square analyses will be used to determine whether there are statistical differences between participant groups in the experimental and control condition at T0.

Increases in knowledge, empathy, and self-efficacy will be assessed using linear mixed effects modeling. Condition will be entered as a fixed effect and intercepts for participant and care center as random effects. Demographic variables will be included as a covariate in the analysis if significant between-group differences are found at T0.

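### Demographic covariates enter the mixed model when a T0 chi-square test is significant, so the primary model depends on chance imbalance and not on what predicts the outcome

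*Protocol article*

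**What the plan says.** Under Data analysis, the protocol article says that demographics are recorded as categories and that "chi-square analyses will be used to determine whether there are statistical differences between participant groups in the experimental and control condition at T0". It then fixes how the result is used: "Demographic variables will be included as a covariate in the analysis if significant between-group differences are found at T0". The candidates appear under Demographics (T0) as an open list: "such as age, sex, level of education, work experience, and the relationship to the person with ID". No other route by which a demographic could enter the model is given.

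The outcome model is a linear mixed model: "Condition will be entered as a fixed effect and intercepts for participant and care center as random effects". Knowledge, empathy and self-efficacy are each measured at T0, T1 and T2. Under Study design, parents/relatives and professionals form two trials that are analyzed separately, so the rule is applied twice.

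On allocation, the Randomization section says "Cluster randomization among locations of the care centers will be used to prevent crossover effects between professionals and parents/relatives" and "Randomization of participants will occur after enrollment but before the baseline assessment". The units are group homes and activity centers.

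**The concern.** When allocation is random and follows enrollment, the null hypothesis of a baseline test is true by design. A significant result tells us that chance produced an imbalance. It does not tell us whether the variable matters. Adjustment gains precision through the relation between covariate and outcome, which this rule never looks at. A strong predictor with a non-significant imbalance stays out, and an irrelevant variable with a small p-value goes in.

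The chi-square test treats participants as independent, although whole locations are allocated. If people at one location resemble each other in age, education or experience, the test will flag differences more often than its nominal level.

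At stake are an analysis that is not settled until T0 data have been seen, possibly different adjusted models in the two trials, and precision given up where a demographic is prognostic.

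**Working it through.** The protocol gives no figure for how this rule behaves, so there is nothing to reproduce. The check asks how often the rule changes the model when randomization has worked, and what it misses.

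**Inputs from the protocol article.** Five named demographics; two separately analyzed samples; 100 participants per sample, half in each condition, so about 50 per arm; target effect 0.5 SD. For the study, "The desired power is set to a minimum of 0.90 and α = .05".

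**Assumptions, not in the protocol.** The level of the T0 tests is not stated and is taken as .05. The demographics are treated as binary and mutually independent. Covariate ICC within location is .05 to .2, with 5 or 10 participants per location. The ICC of .2 under Sample size refers to care centers, so it is not evidence about demographics within locations.

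**1. Chance that at least one covariate enters, no clustering.** 1 - (1 - .05)^k:
- one sample, k = 5: 1 - .95^5 = .226
- both samples, k = 10: 1 - .95^10 = .401

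**2. The same with clustered demographics.** The approximate per-test rate is 2[1 - Φ(1.96/√DE)], with DE = 1 + (m - 1) × ICC. The simulated rates come from 20,000 runs of an unadjusted chi-square under cluster allocation (100 participants, 30% prevalence).

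| Per location (m) | Covariate ICC | DE | Per test, formula | Per test, simulated | Any of 5, simulated |
|---|---|---|---|---|---|
| 5 | .05 | 1.20 | .074 | .072 | .31 |
| 5 | .1 | 1.40 | .098 | .100 | .41 |
| 5 | .2 | 1.80 | .144 | .143 | .54 |
| 10 | .05 | 1.45 | .104 | .103 | .42 |
| 10 | .1 | 1.90 | .155 | .156 | .57 |
| 10 | .2 | 2.80 | .242 | .252 | .77 |

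Formula and simulation agree closely.

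**3. What the test misses.** Take 50 per arm and a characteristic present in 30% versus 45%, ignoring clustering. The pooled proportion is .375, and 1.96 × √(2 × .375 × .625/50) = .190. The standard error under the alternative is √((.21 + .2475)/50) = .0957. The chance of flagging is Φ((.150 - .190)/.0957) = .34, so about two in three such imbalances go unadjusted. For 30% versus 50% it is .53.

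If the factor is worth an assumed 0.5-0.8 SD, a 15-point imbalance moves a plain between-arm comparison by .15 × .5 = .075 to .15 × .8 = .12 SD. That is 15-24% of the 0.5 SD target. It is a shift in a given realized sample, not a bias over repeated randomizations.

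**4. Power and type I error.** The setting is simplified: 50 per arm, one post measure, true effect 0.5 SD, one binary covariate with an assumed 0.8 SD effect, no clustering, 4,000 runs. Power was .69 with no covariate, .70 with the T0 rule and .76 with the covariate always included. These compare strategies and do not estimate this trial's power. Across the null settings, with and without covariate clustering, the rule rejected in .042-.051 of runs.

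**5. Dependence on the tested effect.** With complete data and a random participant intercept, a time-constant covariate cancels out of the within-person change. In a simulated data set with three waves, 50 per arm and a 0.8 SD covariate at 30% versus 50%, the condition-by-time contrast was 0.5315 (SE 0.1653) both with and without the covariate. In a model with condition as the only other fixed effect, the condition estimate moved from 0.446 to 0.310 when the covariate was added.

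**The case against.** Several arguments for the plan have force.

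- **Inference remains valid.** A reader might infer that selecting covariates on T0 tests makes the p-values wrong. The simulation does not support that: type I error stayed at .042-.051. In its most clustered setting with a prognostic covariate, no adjustment gave .086, the rule .051 and fixed inclusion .052, so the rule did no harm there. This stands.
- **The effect may be tested as a change.** The article speaks of increases. If that means a condition-by-time contrast, a demographic main effect hardly matters (step 5). This stands as a limit on size. However, condition is the only fixed effect named, and in that model the covariate does matter.
- **T0 scores and care center are already handled.** A reader might infer that baseline outcome information is ignored. T0 is one of the three repeated measures and care center has a random intercept, so that inference fails. Nor can the .62-.72 test-retest range be used to size a gain from T0 adjustment across outcomes, because the article gives it for the Interpersonal Reactivity Index subscales only.
- **Categories are how the data are recorded.** A reader might infer that age and experience are coarsened to permit a chi-square test. The text runs the other way: recording is categorical, so chi-square is used. The Data recording section also limits the detail collected, so numeric recording is not asked for here.
- **The wording is conditional, not exclusive.** The article does not say that covariates enter in no other way, and a separate analysis plan may name some. But this rule is stated, so it is not a detail left open, and fixed covariates elsewhere would not remove it.

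No evidence in the article shows that any of the demographics is prognostic. The precision loss is therefore conditional.

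**Conclusion.** The point holds as a badly chosen rule that is stated in the plan. The primary model depends on chance imbalance, through a test that is described without allowance for the randomized locations, and the two trials may end with different covariates.

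At least one of the five named demographics would enter by chance in about 23% of samples, or 40% across both trials, given .05 per test and independence. With clustered demographics it is roughly 31-77% per sample over the assumed ICC and location sizes. Correlated demographics would change these figures, and the open list could raise them.

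The supported harms are an analysis not fixed in advance and lost precision where a demographic is prognostic (.70 against .76 power in one favorable illustration). Invalid inference is not shown. The loss is small if the effect is a condition-by-time contrast. The change should be made, but the trial does not stand or fall on it.

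**What to change.** Delete the significance rule. Name in advance a short list of demographics that are already collected and judged prognostic: for example age category and education in both samples, plus work experience for professionals and relationship to the person with ID for parents/relatives. Include them whatever the T0 comparison shows. Report T0 characteristics by arm descriptively, without p-values.

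State how T0 scores are used. Either keep them as one of the repeated outcome measures, or use T0 as a covariate with only T1 and T2 as outcomes, but not both.

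The cost is a change of wording and a few degrees of freedom in each sample of 100. No new data are needed. The Trial status section places the start of data collection after the protocol version date, so the change could be made before any outcome data exist.

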## Discussion

Persons with ID have extra need for secure relationships with primary caregivers but can find making connections difficult. This study aims to explore the effect of a non-invasive m-learning intervention on the empathy and self-efficacy of caregivers, in view of improving attachment relationships with their family member or client with ID.

The m-learning is designed to teach or remind parents/relatives and caregivers of the importance of secure attachment relationships and to improve awareness of the perspective of their child or client. By increasing caregiver understanding of these topics, we expect that empathy and self-efficacy may grow, leading to better care and less stress in social interactions. To maximize the possible effect, the content was compiled in collaboration with parents/relatives and care professionals. The HiSense APP-ID is an m-learning intervention that can be done independently on any digital device and takes up little time. Thus, the intervention is suitable for adding to existing educational programs or as a periodic refreshment course for professional caregivers. The course is also easily accessible for family members of persons with ID. Furthermore, repeated exposures to information over a period of time can improve long-term learning gains [34].

At the same time, it remains to be seen whether independent participants will commit for the full duration of the course of 30 days or more. Automatic reminders will be sent to motivate participants, but some additional extrinsic motivation may be needed for them to finish the course, such as discussing the information with co-workers or with their partner. In addition, the content of the course is strictly theoretical despite its practical examples and recommendations. Participants must relate this information to daily practice and correctly apply their knowledge in new situations. In the case of questions, they may require the advice of a psychologist or behavioral scientist, such as a clinician at the care facility to which they are connected.

A practical concern may be that participants are not blind to their condition, which may cause bias in their responses on the questionnaires during the second measurement. However, test leaders are unaware of the condition of participants.

Because of a close collaboration with three large Dutch care centers in this project, the intervention can be implemented quickly if it proves effective. From the researchers’ point of view, the collaboration is helpful in offering the intervention to the target audience. From the parent and caregiver point of view, it is advantageous to be offered an evidence-based intervention that makes scientific literature on attachment theory available to them in small, practical portions.

In conclusion, the HiSense APP-ID can be a useful instrument for improving attachment relationships between persons with mild or moderate ID and their caregivers. Increased knowledge with regard to attachment theory may improve self-efficacy and empathy in parents/relatives and professional caregivers. Improving their basic knowledge may reduce stress and prevent the development of problematic behavior arising from a lack of experienced security in persons with ID.

## Trial status

Protocol version 1, dated 5 January 2018. The intervention has been developed. Recruitment of participants started within the participating care centers in October 2017, and data collection is planned to start in February 2018.
